Furthermore, the timing of sound-related interventions should be strategically planned not only to align with each infant’s individual feeding and sleep-wake cycles [36] – as these factors can potentially interfere with the beneficial effects of musical interventions – but also to ensure they occur during quieter periods in the NICU, allowing for safe and effective delivery [14]. In particular, live singing interventions must be carefully calibrated and monitored to stay within safe sound limits set by medical regulations (see [32]). These regulations generally stipulate that sound levels outside the incubator should not exceed a continuous average of 45–50 dB, with transient peaks not surpassing 65 dB. Unfortunately, even highly trained professional singers, when attempting to maintain the lowest possible sound pressure levels (SPLs), may still exceed these limits. A study by Akerlund & Gramming [37] found that trained female singers could only produce minimum SPLs around 51.5 dB at low pitches, which already slightly exceeds the upper recommended continuous sound level in NICUs.

Finally, a seamless integration of any musical intervention into the infants’ overall care regimen requires close coordination with the medical team, as this collaborative effort is vital for aligning the intervention sessions with the already established medical protocols and tailoring them to meet the specific health requirements and medical conditions of each infant [38]. Such integration helps to ensure that the music intervention sessions are not only safe but also effectively support the broader therapeutic goals set forth by the healthcare providers, which especially in this sensitive and demanding in terms of physical development context require the parental involvement as another critical aspect according to the latest clinical research [39,40].

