**Fig 2 pone.0328211.g002:**
[figure not shown]
Study Protocol Flow Chart.

In this design, although the EEG will be the primary tool of data collection and analysis, the rationale for incorporating video data is multifaceted. Firstly, the video recordings will complement the electroencephalogram (EEG) recordings in offering a comprehensive parallel view of the infants’ neural and behavioral responses. Furthermore, the videos will serve as a tool for quality control by ensuring that the prescribed research protocol is uniformly followed by all facilitators, contributing to the scientific integrity of the research. Finally, the videos will allow for a later examination of any synchrony or coordinated interactions between the infant and the facilitator, shedding light on phenotypical – not able to be measured by the EEG – aspects of the intervention.

The live singing intervention will be delivered by four different profiles of individuals-facilitators: a male music therapist, a female music therapist, the mother, and the father of the newborn. During the delivery of the intervention (explained in more detail below), there will be five ‘conditions’ measured: Silence1 (180 seconds), Note A (60 seconds), Silence2 (180 seconds), Song (90 seconds) and Silence3 (180 seconds).

It is important to note that the study protocol will be conducted in a dedicated room, largely isolated from the ambient noise typically found in the rest of the NICU. This aspect of the study design is crucial for two main reasons:

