Firstly, it will ensure the comfort and safety of the participating newborns. All actions taken in the context of the NICU require adherence to the recommended standards for the NICU sound environment. Therefore, the importance of a well-managed acoustic environment in reducing stress and discomfort for our participating infants is of paramount importance. Such a consideration has been consistently highlighted both for clinical and research settings alike [32] and a sound-controlled room within the NICU seems to be the only viable option for achieving the necessary level of sound management for our participants, without disrupting other clinical operations. More specifically, in the NICU context, when considering the operational sound as outlined by White, Smith, Shepley, et al. [31], the combination of continuous background sound and operational sound should not exceed an hourly L_eq_ of 45 dB and an hourly L_10_ of 50 dB, both A-weighted slow response, with transient sounds or L_max_ not exceeding 65 dB. Our study, with sound exposure lasting less than 3 minutes per hour, will strictly adhere to these guidelines. However, the transient nature of singing, distinct from the continuous and better-controlled sound pressure levels typically found in continuous speech, might lead to brief instances where we slightly exceed these thresholds by about 15 dB. According to evidence, even professional singers, and more so untrained individuals like the parents participating in our study, are not able to produce transient peak Sound Pressure Levels (SPLs) below 78–79 dB when singing softly [70]. However, it has been noted that in environments with lower ambient noise, humans can more easily maintain a soft vocal output because the reduced background sound allows for greater control and minimizes the need to compensate with higher volume [71]. Therefore, we believe that a dedicated room will significantly aid in ensuring the correct application and viability of the aforementioned recommendations – by providing an acoustically controlled setting that minimizes ambient noise and facilitates softer singing performance – as compared to the open NICU floor, thus preventing the intervention from inadvertently exceeding the recommended soundscape limits.

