### Intervention

Preterm newborns who meet the inclusion criteria will be exposed to a specific, in terms of content and exposure timing, live singing intervention four times in a calendar week – once per day. The decision to implement the intervention four times per calendar week was informed by a critical framework evaluation of clinical and practical constraints outlined in Dimitropoulos [90]. According to this evaluation, conducting the intervention more frequently (e.g., 5 times/week or more) could induce excessive stress on infants and caregivers, raising ethical concerns and logistical challenges for maintaining caregiver involvement within the hospital setting beyond one week. Conversely, a lower frequency (e.g., 3 times/week or fewer) is not feasible due to the study’s design, which explicitly involves four distinct facilitator profiles (mother, father, male music therapist, female music therapist). In addition, by conducting the intervention in the proposed way, we expect to observe and record the immediate and short-term neurophysiological effects of the musical stimuli on the infants’ brains, while ensuring that the data reflects the true impact of the intervention, free from external variables that might arise from a more prolonged or sporadic schedule. Furthermore, the specific exposure over this consistent period will facilitate a comprehensive understanding of any cumulative or evolving effects of the intervention across consecutive sessions, allowing for a detailed analysis of the EEG baselines recorded each one of the four times the intervention is delivered.

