### Outcomes and statistical analysis

To rigorously evaluate the effects of our live singing intervention, we decided to employ a series of advanced statistical methods tailored to the specificities of the study design and data characteristics. The complete analysis focused on the EEG-based outcome measures, with an emphasis on Spectral Power (primary outcome) and Spectral Entropy (secondary outcome), across the Delta frequency band.

Special attention was given to the Delta frequency band as it is widely recognized for its relevance in neonatal brain activity [99–100]. The Delta frequency band, typically ranging from 0.5 to 4 Hz, is the slowest of the EEG frequency bands and is a critical marker of brain maturation. Higher absolute power in the delta frequency band has been associated with more favorable long-term neurodevelopmental outcomes, reflecting the progression of underlying neural processes during early development [99]. Given its prominence in this context, we believe that the Delta frequency band can be an essential marker for assessing the impact of sound and music on the neurophysiological state of our participants, providing in result critical insights into how these infants process auditory stimuli and the extent to which our intervention influences brain activity patterns.

More specifically to the design of our statistical analysis process and given the study’s repeated measures design and the nested data structure (with multiple observations per infant), a mixed-effects model was decided to be employed to analyze first the Delta Spectral Power, allowing for the inclusion of both fixed effects (conditions and facilitators) and random effects (variability across individual infants), while also meticulously fitting the model to account for the inter-individual variability after isolating the impact of the different intervention conditions and facilitator profiles.

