Considering the sensitivity of the particular context, and to further protect the participants’ privacy and confidentiality, all collected data are de-identified and pseudonymized at the source (i.e., embeded function of the **nëo™** EEG monitoring unit during the extraction process), with each dataset assigned a unique identification number. Personal identifiers, such as names, are not linked to the data in any study analysis, report, or publication phase, while parents are informed of their right to access the data collected from their infants at any time. Once parents have received all relevant information and have had their questions answered, they are asked to provide written consent, indicating their agreement to participate in the study.

At this point, we should mention that despite its non-invasive nature, the study recognizes potential risks, such as the overstimulation of infants due to sound exposure and stress related to handling. To mitigate these risks, sound levels are closely monitored using a dB dosimeter – as already mentioned – and interventions are scheduled in this way so to ensure adequate rest periods for the infants. It has already been pointed above that the study is conducted in a specially designated, quiet room within the NICU to minimize stress, while moreover, the application of EEG electrodes, a key part of the study, is performed by specialists trained in neonatal care, further reducing the risk of discomfort or stress for the infants. In case of any unforeseen medical complications or adverse reactions, the study protocol includes provisions for the immediate cessation of the intervention and prompt medical evaluation, ensuring the safety of the participants.

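### The short singing time does not establish the promised adherence to the hourly Leq, hourly L10 and Lmax sound limits, and the same paragraph expects those limits to be exceeded

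*Protocol article*

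**What the plan says.** All references are to the protocol article.

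- **Limits (Methods, Study design).** For background and operational noise taken together, the level "should not exceed an hourly L_eq_ of 45 dB and an hourly L_10_ of 50 dB". The third limit is on peaks: "with transient sounds or L_max_ not exceeding 65 dB". The first two limits are A-weighted with slow response.
- **Adherence claim (same paragraph).** "Our study, with sound exposure lasting less than 3 minutes per hour, will strictly adhere to these guidelines"
- **Expected exceedance (the sentences that follow).** Singing may briefly pass the thresholds by about 15 dB. Even professionals singing softly are said not to produce peaks below 78–79 dB, and untrained parents are expected to find it harder. The paragraph ends by saying that the dedicated room will keep the intervention from exceeding the limits.
- **Introduction (Delivering (live) music interventions in the NICU).** A continuous average of 45–50 dB is given, with peaks to 65 dB and no averaging window. It is applied to the singing itself, in that women with vocal training "could only produce minimum SPLs around 51.5 dB at low pitches, which already slightly exceeds the upper recommended continuous sound level in NICUs".
- **Timing.** The conditions are "Silence1 (180 seconds), Note A (60 seconds), Silence2 (180 seconds), Song (90 seconds) and Silence3 (180 seconds"), and the Intervention section gives the "live singing intervention four times in a calendar week – once per day".
- **Monitoring.** A dB meter stands in the room (Study design), and under Ethics "sound levels are closely monitored using a dB dosimeter". Neither place gives an averaging window.

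**The concern.** The article names the harms it wants to avoid: stress responses and inner-ear hair-cell damage in the Introduction, and overstimulation under Ethics. Adherence to the sound limits is its stated protection, and the reason offered is that exposure is under 3 minutes per hour.

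That reason does different things to the three limits. It makes hourly L10 almost blind to the singing. It lowers hourly Leq by a fixed amount without showing that the result is below the limit. It has no bearing on Lmax, because a maximum does not fall when the rest of the hour is quiet. Meanwhile the Introduction judges the sung level directly, so the article holds two yardsticks that can disagree about the same singing.

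At stake is whether a reader can take the adherence statement as a property of the design. No EEG outcome or analysis is affected.

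**Working it through.** **Inputs from the article.** NoteA 60 s; Song 90 s; one session per day; limits of hourly Leq 45 dB, hourly L10 50 dB and Lmax 65 dB; 51.5 dB as the softest level of trained female singers; 78–79 dB as the lowest peaks of soft singing.

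**Inputs assumed.** The room's background level B and the mean sung level L at the meter are not given, so ranges are shown.

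**1. The article's exposure figure.** 60 + 90 = 150 s = 2.5 min, with one session per day. The figure of under 3 minutes per hour is reproduced. Share of the hour: 150/3600 = 4.17%.

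**2. L10.** This is the level exceeded for 10% of the hour, or 360 s. Singing supplies 150 s. Over a steady background it cannot change L10, however loud it is. Over a varying background, 360 − 150 = 210 s must come from the other 3450 s, so the reading moves only from the background's 10% exceedance level to its 210/3450 = 6.1% level.

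**3. Hourly Leq.** Leq = 10·log10[(150·10^(L/10) + 3450·10^(B/10))/3600]. With negligible background, Leq = L − 10·log10(3600/150) = L − 13.8 dB.

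| Sung level L (dB) | Hourly Leq, negligible background (dB) |
|---|---|
| 51.5 | 37.7 |
| 55 | 41.2 |
| 58.8 | 45.0 |
| 60 | 46.2 |
| 65 | 51.2 |

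Solving for the highest sung level with Leq at 45 dB:

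| Assumed background B (dB) | Highest sung level that passes (dB) |
|---|---|
| negligible | 58.8 |
| 35 | 58.4 |
| 40 | 57.2 |
| 42 | 56.0 |
| 44 | 52.6 |
| 45 | none above 45 |

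Taken at face value, the 51.5 dB example exceeds the Introduction's limit, yet passes hourly Leq with a quiet background and leaves L10 unmoved.

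**4. The cited peaks.** The time at level P that alone brings hourly Leq to 45 dB is 3600·10^((45 − P)/10). For P = 78 this is 1.8 s; for P = 79 it is 1.4 s. If such levels lasted that long in total, the Leq limit would be reached despite the short exposure.

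**5. Lmax.** 78 − 65 = 13 dB and 79 − 65 = 14 dB, roughly the article's own 15 dB. On its own figures the 65 dB limit is expected to be exceeded.

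**The case against.** Several points on the other side stand.

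- **No hourly verdict is planned.** The article cites a standard and says it will be followed. Nowhere does it say that hourly Leq or L10 will be computed, tabulated or used to declare the exposure safe.
- **The hourly window belongs to the cited standard.** An hourly measure cannot be faulted for averaging over an hour. What can be faulted is offering brevity as the ground for adherence.
- **Lmax does register singing**, and the article openly expects it to be exceeded. A breach is therefore not concealed.
- **Other noise can move L10**, since the limit covers background and operational sound together.
- **The Introduction paragraph is background.** It gives no averaging window and is not declared the trial's acceptance limit. The distance and weighting behind the 51.5 dB are not stated, nor is the facilitators' distance from the cot, so the levels may not be comparable.
- **An article may leave an exposure table to the full protocol.** That "The complete analysis focused on the EEG-based outcome measures" is not in itself a fault.

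A reader might infer that the study will declare its sound exposure within guideline from hourly averages that hide what the infant heard. The first, third and fourth points show that the document does not support this. Nor does it show that infants will be overexposed, because no mean sung level is given.

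None of these points rescues the adherence claim. It covers all three limits and gives short exposure as its ground, and the sentences after it contradict it.

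**Conclusion.** The point holds as a minor one. The design does not deliver the stated strict adherence on the article's own figures. Brevity makes L10 nearly uninformative about the singing (150 s against 360 s), leaves Leq dependent on an unstated sung level, and does nothing for Lmax, which is expected to be exceeded. The Introduction and Study design also apply the continuous limit on different time scales.

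The 4.17% share and the 13.8 dB offset follow from the article alone. The 57–59 dB range assumes a background of 40 dB or lower; it narrows at louder backgrounds and vanishes at 45 dB. The 51.5 dB contrast assumes comparable distance and weighting. The 1.4–1.8 s figure treats cited peaks as if they were energy-average levels, which the article does not establish.

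**What to change.** 1. In Study design, remove or qualify the statement of strict adherence and the under-3-minutes argument, so that it agrees with the exceedance expected in the next sentences and with the paragraph's closing claim about the room.
2. Reconcile the Introduction and Study design on the averaging window to which the continuous limit applies. The investigators decide which; no sound limit is proposed here.
3. From the meter already in the room, describe Leq and Lmax for the NoteA and Song blocks by facilitator, alongside any hourly figure, and state the measuring position and weighting.

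The cost is a few sentences and one descriptive table, provided the meter stores readings that can be matched to the blocks, which the article does not say. No extra infants, staff or procedures are needed. The downside is that the reported exposure will look less favourable than an hourly average.

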Secondly, recent research, including a study by Restin et al. [72], indicates that incubators can be significant sources of noise, especially in the open environment of the NICU floor. To mitigate this issue, we plan to use an open cot/radiant warmer (as depicted in Fig 3) in the dedicated room when applicable, or alternatively, bring the entire incubator into the room. This approach will help minimize or eliminate noise from the incubator that might reach the infant. As an additional precaution to all the above, a dB measuring device will be also stationed in the dedicated room, outside the incubator where applicable, to monitor noise levels throughout the intervention.

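### The Study design section claims strict adherence to sound limits that include a 65 dB maximum, while its own figures put singing peaks 13 to 15 dB above it

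*Protocol article*

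**What the plan says.** All of the central text is in the noise-control discussion of the Study design section.

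- **Limits.** For the hourly average, "the combination of continuous background sound and operational sound should not exceed an hourly L_eq_ of 45 dB". The hourly L10 limit is 50 dB, and the list ends "with transient sounds or L_max_ not exceeding 65 dB".
- **Adherence claim.** The study, "with sound exposure lasting less than 3 minutes per hour, will strictly adhere to these guidelines".
- **Concession.** Singing "might lead to brief instances where we slightly exceed these thresholds by about 15 dB". The article adds that professionals, and still more so untrained parents, cannot keep transient peaks under 78–79 dB even when singing softly.
- **Closing claim.** The dedicated room is expected to allow softer singing than the open NICU floor, "thus preventing the intervention from inadvertently exceeding the recommended soundscape limits".
- **Monitoring.** Later in the same section, "a dB measuring device will be also stationed in the dedicated room". The Ethics section repeats that sound levels are monitored.

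The Introduction, under Delivering (live) music interventions in the NICU, gives a similar warning: "even highly trained professional singers, when attempting to maintain the lowest possible sound pressure levels (SPLs), may still exceed these limits". It cites a study in which "trained female singers could only produce minimum SPLs around 51.5 dB at low pitches".

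**The concern.** Strict adherence, an acknowledged excess of about 15 dB, and prevention of exceedance cannot all be true of the same 65 dB maximum. The reason attached to the adherence claim is short exposure. Short exposure helps with limits that average or rank sound over an hour, but it does nothing for a maximum, which a single loud instant can break.

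This is a safety statement about infants whom the article describes as extremely sensitive to sound, and the Introduction links the limits to stress responses and damage to inner-ear hair cells. The article also offers itself as a methodological template, so others may copy the claim. What is at stake is what the trial can say about guideline compliance.

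**Working it through.** **Inputs from the article**
- Singing time per session: Note A 60 s and Song 90 s (Study design), one session per day (Intervention).
- Limits: hourly Leq 45 dB, hourly L10 50 dB, Lmax 65 dB (Study design).
- Lowest soft-singing peak: 78–79 dB. Conceded excess: about 15 dB (Study design).
- Minimum level of trained female singers at low pitch: 51.5 dB (Introduction).

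**Assumptions.** The article gives neither the background level in the room nor the mean level during singing. I use no background, 40 dB and 44 dB for the first, and 51.5, 55 and 60 dB for the second.

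**1. The article's own figures reproduce.** Exposure is 60 + 90 = 150 s = 2.5 min, which is under 3 minutes per hour. The peak excess is 78 − 65 = 13 dB to 79 − 65 = 14 dB, in line with the stated 15 dB, which would mean peaks of 65 + 15 = 80 dB.

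**2. Lmax.** Duration does not enter. At 78–80 dB the 65 dB limit is exceeded by 13 to 15 dB, however short the singing.

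**3. Hourly L10.** This is the level exceeded for 10% of the hour, or 360 s. Singing takes 150/3600 = 4.2%. Other sound would have to exceed 50 dB for at least 360 − 150 = 210 s of that hour to break the limit. Singing alone cannot do it, so here the article's reasoning is sound.

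**4. Hourly Leq.** With L the mean level during singing and B the background in the other 3450 s:

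Leq = 10·log10[(150/3600)·10^(L/10) + (3450/3600)·10^(B/10)]

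With no background, 150 s in an hour lowers the singing level by 10·log10(3600/150) = 13.8 dB. Setting Leq = 45 dB gives the highest permitted L:
- No background: 45 + 13.8 = 58.8 dB.
- B = 40 dB: 57.2 dB.
- B = 44 dB: (31,622.8 − 0.9583 × 25,118.9) × 24 ≈ 181,212, so L = 52.6 dB.
- B = 45 dB: the ceiling falls to 45 dB, because the background alone uses the whole allowance.

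Hourly Leq for chosen singing levels:

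| Mean level during singing | No background | B = 40 dB | B = 44 dB |
|---|---|---|---|
| 51.5 dB | 37.7 | 41.9 | 44.8 |
| 55 dB | 41.2 | 43.6 | 45.7 |
| 60 dB | 46.2 | 47.1 | 48.2 |

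The 45 dB limit is kept throughout at 51.5 dB, broken only at the 44 dB background at 55 dB, and broken in every column at 60 dB. The 51.5 dB figure is a minimum for trained singers, so it does not show where untrained parents would fall.

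**The case against.** The strongest reply is that nothing is hidden. The exception follows the commitment in the very next sentence, with its size and reason, and the Introduction gives the same warning. A charitable reader takes the text as adherence apart from brief peaks, with the short-exposure clause meant for the hourly limits only. The closing sentence is also hedged: it is a belief, a comparison with the open NICU floor, and about inadvertent excess. The Leq scenarios rest on levels that the article does not give, and the only non-peak singing level it does give keeps the limit at backgrounds up to 44 dB. The measuring conditions behind 78–79 dB are not shown, so the level at the cot may be lower. A numeric operating ceiling could reasonably sit in the full protocol.

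Much of this stands. The excess is disclosed, L10 is secure against singing alone, Leq is unverified and not shown to be broken, and the exposure at the infant is unknown. The absence of a numeric ceiling is not itself a fault.

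Two things survive. The adherence sentence is unhedged and refers to a list that includes Lmax; disclosure of the excess contradicts that sentence and does not qualify it. And while the article supports the view that a quiet room helps people sing more softly, it gives no figure showing that the room closes a gap of 13 to 15 dB.

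**Conclusion.** The concern holds, as a minor point. For Lmax the adherence claim is wrong by the article's own estimate, by 13 to 15 dB. For L10 the short exposure is an adequate reason as far as singing is concerned. For hourly Leq the claim may be true but is not established: it depends on a mean singing level and a background that are not given. The 52.6 to 58.8 dB ceilings illustrate that dependence under assumed backgrounds and are not limits taken from the article.

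The Lmax conclusion takes the authors' comparison of singing peaks with the limits at face value. It shows an inconsistent safety statement, not a measured exposure at the cot. The EEG outcomes, sample size and analysis are untouched.

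**What to change.** In the noise-control paragraph of the Study design section:

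1. Withdraw strict adherence for Lmax. State that transient peaks above 65 dB, by about 15 dB on the authors' estimate, are anticipated during singing and that the level at the infant is uncertain.
2. State that 150 s of singing cannot by itself break the hourly L10 limit.
3. Make the hourly Leq statement conditional on measured levels.
4. Say that the dedicated room reduces the extent of any exceedance, in place of saying that it prevents it.
5. Report measured Lmax and hourly Leq from the dB device already placed in the room, so that any compliance statement rests on data.

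The cost is a few words in one paragraph and one reporting item. The intervention, room and schedule do not change.
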